**Anticipated Products/Interventions and Use**

Findings from this intervention can be used to help guide web-based HIV prevention efforts. Further, the information from this intervention has tangible benefits to drug prevention and sexual risk reduction efforts nationally. Information from this intervention will better inform public health agencies about the magnitude of these behaviors and help them to develop outreach and prevention strategies that address the needs of MSM who use the Internet from their states. The end-product of the work will be a standardized protocol ready for internet-based intervention trials to have significant reach among MSM online.

**Notifying Participants of Study Findings**

There will be a message at the end of the survey, notifying participants that the study findings will be available on the Public Health Solutions website in the coming year. The Public Health Solutions website address will be listed.

**Dissemination of Results to Public**

Findings will be disseminated at domestic and international scientific meetings and through peer-reviewed publications. We will also disseminate our research findings via local and national media and make study findings available for participants and other interested individuals as an online downloadable report on Public Health Solutions website. Pulse Studies (synopses of previous online and offline Public Health Solutions studies) are available on the Public Health Solutions website and are distributed to more than 1,000 elected officials, public health professionals, policy makers, service providers, advocates and media outlets. Findings will also be presented to the community via discussion groups and forums.

# IV. REFERENCES

**APPENDIX A.**

**ONLINE INTERVENTION PILOT / FORMATIVE WORK**

In October 2005, MHRA, in collaboration with New York University ([name] [name]), conducted a national online behavioral intervention pilot on Manhunt.net. An 8-minute dramatic video, **The Morning After**, was designed, written and filmed to promote critical thinking about HIV disclosure, risky sexual behaviors and the complex beliefs and attitudes underlying these behaviors. For this proposed project, The Morning After dramatic video will serve as an intervention for sexual risk reduction within the context of alcohol use.

**Dramatic Video, The Morning After:** The approach we used for this video is grounded in traditional social cognitive theory, which has been successful in many other educational settings. To the best of our knowledge, we are the first to show that it is also successful as an online intervention pilot. The evaluation of our dramatic video was completed in February 2006. MSM were recruited through banner ads on the exit page of Manhunt.net. Over 1,000 men from 48 of 50 states completed a baseline behavioral survey, watched the video, completed the post-video survey, and provided email addresses for a 3 month follow-up.

**Description of The Morning After:** Directed by [name], this pilot video vignette was produced for the HIV Is Still A Big Deal Project (MHRA & NYU, 2005). This 8-minute dramatic video is a fictional story with carefully crafted plot and characters based on reality. This vignette tells the story of four gay friends, and focuses on two of them. Josh awakens the morning after excessively drinking and hooking-up with Eric to find antiretroviral medications in Eric’s bathroom. He quickly finds his friends to talk about this, after which Eric arrives to talk with Josh as well. In the course of this short drama, issues of disclosure (“asking” and “telling”), alcohol use, condom use, and HIV testing are expressed in the situation and the conversation.

***Title: Is HIV Still a Big Deal?***

***Baseline***

[name], PI

Between October 11 and 22, 2005 we conducted our first national online behavioral intervention on Manhunt.net (funding from the van Ameringen Foundation, The New York Community Trust, and The Shelley and Donald Rubin Foundation). **The Morning After** was designed to promote critical thinking about HIV disclosure, risky sexual behaviors and the complex beliefs and attitudes underlying these behaviors. Approximately 13,500 men clicked on the online banner ad, and out of those, 3,139 consented to participate in the intervention; 2,777 completed the baseline behavioral risk survey (pre-test); 1601/2777 watched the video about a sexual encounter between an HIV-positive and HIV-negative male; 1510/1601 completed the questions about HIV testing and disclosure after the video (post-test); and 1087/1510 consented to give us their email address for a follow-up behavioral risk survey in 3 months. Online, 1,002 men completed the baseline behavioral survey, watched the video, completed the post-video survey and provided valid email addresses for 3 month follow-up. The median age of men consenting to participate was 38.

***Follow-up*: Validation of the Online Video as an Intervention**

Of the 1,002 men who completed the survey and provided emails, 3 months later, 908 emails were still working. Emails linking to the follow-up survey were sent 1/17, 1/23 and 2/1/06 to 908/1,002. No incentives were provided. Preliminary analysis compared disclosure of HIV status to sexual partners and HIV testing, before and in the 3 months after watching the video, by McNemar and Pearson Chi-square tests. Three months after watching the video, 496 of 908 men (55%) with working emails completed the follow-up survey. Men completing follow-up and those who did not were similar by race/ethnicity (14% Hispanic, 72% white, 6% black, 2% Asian, 6% mixed/other), age (mean 38) and prevalence of unprotected anal intercourse with a new/casual partner (36%), but were significantly more likely to have a college degree (55% vs. 47%, p=.01). Statistically significant behavior changes were found. Men were 3 times more likely to ask their partner’s HIV status (OR=3.0, p<.001) and two times more likely to disclose their own(OR=2.2, p<.001) at follow-up compared to baseline. The 318 HIV-negative men participating in the evaluation were also three times more likely to report HIV testing during follow-up (42%) than in the 3 months before baseline (20%) (OR=2.8, p<.001). These findings strongly suggest that online interventions designed to engage critical thinking are an efficient and effective way to influence behavior change in large numbers of at-risk MSM.

We examined the prevalence and stability of drug and alcohol use between baseline and follow-up. At baseline, 7% reported methamphetamine use in their last sexual encounter. At follow-up, 5% reported methamphetamine in their last encounter. Out of the methamphetamine users at baseline, 39% followed up and were significantly LESS likely than non-users to follow-up (OR 0.6, p<.05). Contrary to methamphetamine use, other drug use (i.e., poppers, marijuana, MDMA, GHB, cocaine) as well as alcohol use, reported between baseline and follow-up remained stable. Specifically, there were no significant differences in the proportions of men reporting drug or alcohol use at baseline compared to follow-up. Drug use at baseline and follow-up was 24% and 32%; alcohol use was 27% at both baseline and follow-up.

**ONLINE RESEARCH STUDIES**

***Study 1:* Web-based Survey of Sexual Behavior among Gay and Bisexual Populations**

[name], PI

Between June 3 and July 24, 2002 an anonymous, cross-sectional online survey was conducted, inquiring about general sexual and drug-using behaviors among MSM during a recent 6-month period. The survey was displayed in the chat room area of a gay-oriented website.24, 54, 55 Approximately 6,000 participants clicked on the banner; 2,284 exited the survey without answering any questions; 2,915 men who completed the survey reported sex with other men or self-identified as gay or bisexual. Participants resided in all fifty states. The sample was predominately white (85%). Nearly half of the sample was between 18 and 29 years of age (range 18-60+). Most reported up to $40,000 income and at least some college education or more. Most men (80%) reported having sex only with men. Overall, 8% of the sample reported testing HIV-positive. During the six-month study period 80% reported more than one sex partner. Forty-five percent reported any illicit drug use and about half reported drinking alcohol before or during sex. Approximately 68% of those reporting drug use reported drugs before or during sex. The self-reported HIV prevalence by age group (which included men in the denominator who were not tested during the 6-month period the study asked about) was 2% for 18-24, 6% for 25-29, 12% for 30-39, 10% for 40-49, and 13% for 50 or older.

***Study 3: Viagra, Drug Use and HIV Transmission in Men Who Have Sex with Men***

[name], PI

Between November 2004 and March 2005, we conducted our third anonymous, cross-sectional online study (funded by an independent medical grant from Pfizer, Inc.), inquiring about substance use and sexual risk behaviors with and without pde-5 inhibitors (i.e., Viagra, Levitra, or Cialis) within the past 12 months. Over 19,000 respondents clicked on the consent form, and approximately 11,300 cases were complete enough for statistical analysis. Eight websites hosted banners linking to an anonymous questionnaire, which asked about behavior in the past 12 months. 7,764 men from the US or Canada reported sex with men or both men and women within 12 months prior to the survey. The median age was 38 (range 18-85); 82% were white; 63% earned $40,000 or more; 93% reported sex with only men; 31% reported having a main partner; 61% of men without a main partner met their last sex partner online; 23% reported drugs and 22% reported alcohol before/during sex. Specific drugs reported before/during sex included marijuana (8%), poppers (10%), Viagra/Levitra/Cialis (13%), and crystal methamphetamine (8%). Approximately 14% reported two or more partners in the last encounter. HIV prevalence by age group (which included men in the denominator who reported HIV testing results, N=6,465) was 4% for 18-24, 6% for 25-29, 14% for 30-39, 22% for 40-49, and 19% for 50 or older.

**APPENDIX B. Survey Banner**

[figure not shown]

**APPENDIX D. DESCRIPTION OF ASSIGNED BRANCH CONDITIONS**

**Branch 1** (control): “We will now ask you 6 brief questions.”

**Branch 2** (standard text-based prevention webpage) http://www.cdc.gov/hiv/topics/msm/index.htm:

“Now you will see a text-based HIV prevention website. When you are finished, you will be asked 6 short questions.”

**Branch 3** (Morning After video):

“Now you will see an 8-minute dramatic video about four gay friends. When you are finished, you will be asked 6 short questions.”

**Branch 4** (Talking About HIV video):

“Now you will see a 5-minute documentary video about gay men. When you are finished, you will be asked 6 short questions.”

**Branch 5** (both videos):

“Now you will see 2 brief videos (totaling 13 minutes) about gay men. When you are finished, you will be asked 6 short questions.”

**APPENDIX E. BASELINE / FOLLOW-UP SURVEY (same general survey for both time points with the following exceptions to the follow-up survey described below)**

Please see pdf document ([name] Intervention Survey)

**The following items are included in the baseline survey but excluded from the follow-up:**

I am a... (Gender)

How would you describe your sexual orientation?

Where do you live?

The city that I live in has...

My annual income is:

Are you currently employed?

How many times have you moved in the past year?

Have you ever had oral or anal sex with a male?

Have you ever had oral, vaginal, or anal sex with a female?

Past year / Lifetime Sexual history questions for males and females

About how old were you when you first had a drink?

In your lifetime: have you ever injected...

In your lifetime: have you ever had a blood transfusion?

In your lifetime: have you ever been tested for Hepatitis B?

In your lifetime: have you ever been vaccinated for Hepatitis B?

In your lifetime: have you ever been tested for Hepatitis C?

How many times have you been tested for HIV?

Do you have a primary care provider?

Do you currently have health insurance?

Have you ever spent at least 1 night in jail or prison?

Which best describes your weight?

**The following items are included in the baseline survey but the time period will be modified to the past 60 days for the follow-up survey:**

In the past 60 days...

Have you been diagnosed with the following?

Have you had mental health counseling or treatment from a mental health provider? y/n

Have you attended any alcohol or drug treatment programs (such as twelve-step program)? y/n

(please specify)________

Have you seen an online video about HIV? (check all that apply)

□ Yes, in this study

□ Yes, on Youtube

□ Yes, on another website (please name the site)__________

Following completion of the baseline survey participants will be provided with the following instructions depending upon eligibility to continue further:

If ineligible, the participant will receive a message saying, “Thank you for your time. We appreciate your input in this study. Here are some links to helpful websites about staying healthy. Please check back on the MHRA website in 2008 for a description of the study’s results.”

If eligible, the participant will automatically be directed to the C-2 Consent Form.

**APPENDIX F. POST-INTERVENTION INTENTION QUESTIONS**

| **{ Post Intervention Questions}** | | |
| --- | --- | --- |
| In the next 60 days... | Definitely probably might probably definitely  will will won’t won’t | I prefer not to answer () |
| How likely are you to... |  |
| …ASK your new sex partners their HIV status? | () () () () () |
| …TELL your new sex partners your HIV status? | () () () () () |
| …use condoms with new sex partners? | () () () () () |
| …reduce alcohol use before sex? | () () () () () |
| …reduce drug use before sex? | () () () () () |
| {if negative or untested}  Do you plan to get an HIV test? | () () () () () |  |

“Thank you for participating in the study. In 60 days, we will contact you using the email address you provided to ask you some additional questions. Here are some links to helpful websites about staying healthy.”

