## Protocol Summary

The study was proposed by and extends prior research of Public Health Solutions (please see Appendix A). This protocol describes an Internet-based, five-branch randomized controlled intervention, enrolling 3,000 adult MSM. The five branches include 1) a control condition receiving no intervention content, 2) a standard text-based prevention webpage (from CDC.gov site: http://www.cdc.gov/hiv/topics/msm/index.htm), 3) an 8 minute dramatic video addressing sexual risk reduction within the context of alcohol use (The Morning After), 4) a 5 minute documentary video addressing HIV disclosure, HIV testing, and condom use with the sub-context of drug use (Talking About HIV), and 5) both videos. After completing the baseline survey, eligible participants who consent to participate in the intervention will be randomly assigned to the control condition or one of the four intervention conditions. The control condition will not include the delivery of any intervention content. All participants (branches 1-5) will be asked to complete a brief post-intervention survey (to measure intentions). For those in the control condition, the intentions survey will take place immediately after consent. After the intentions survey, all participants will be automatically directed to an exit page containing links to health related web sites and hotlines. Finally, all participants will be invited via email to complete a final 60-day follow-up survey.

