**Additional Measurements**

Immediately after the intervention activity (or baseline for those who are randomized to branch 1), participants will be asked to complete a brief intentions survey (Appendix F). These questions will focus on HIV disclosure, condom use, alcohol/drug use, and HIV testing (for those who are HIV-negative) in the next 60 days.

Additionally, we will also record the number and categories of link “clicks” that consented respondents make when shown the resource page after completing the post-intervention assessment (baseline) and after completing the follow-up assessment. This page, found in Appendix G, contains links to a variety of health related resources. The data will be automatically added to the individual participant’s data file.

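### The two intention items on reducing alcohol and drug use before sex go to every randomised man with no routing and no not-applicable choice, so a score pooled over all men mixes applicability with intention

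*Protocol*

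**What the plan says.** The Protocol Summary states that "All participants (branches 1-5) will be asked to complete a brief post-intervention survey". The inclusion criteria require recent sex with a man and a new partner, but no alcohol or drug use.

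Appendix F offers five answers, from *definitely will* to *definitely won't*. Two of its six items ask how likely the man is to "reduce alcohol use before sex" and to "reduce drug use before sex". The only way out printed on the form is "I prefer not to answer". The HIV-test item alone carries a condition: "if negative or untested". The section Additional Measurements follows the same pattern, with a condition on testing only: "These questions will focus on HIV disclosure, condom use, alcohol/drug use, and HIV testing (for those who are HIV-negative) in the next 60 days".

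The outcome table (Primary and Secondary Outcome Variables, part headed Additional Variables) lists four intention variables, treated as continuous: condoms, asking, telling and HIV testing. The alcohol and drug items are not among them. Appendix D tells participants to expect six questions.

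**The concern.** To reduce something, a man must be doing it. A man who never drinks before sex may tick *definitely won't* because he has nothing to cut, tick *definitely will* because he agrees with the aim, or decline to answer. The first looks like an unwilling drinker and the second like a motivated one. The form cannot separate them.

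The two videos are set apart partly by their alcohol context (*The Morning After*) and drug context (*Talking About HIV*). These items are the immediate self-report of intention on those two behaviours. If branches are compared on the scores of all men, part of what is compared is how non-users happen to read the question, and any shift among users is averaged with men who have nothing to shift.

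The authors saw this problem for HIV testing and routed that item. The same logic was not carried to these two.

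**Working it through.** The protocol gives no sample size, power or significance level for the intention items, so there is no stated figure to reproduce. The check has three parts.

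**1. Share of men to whom the items do not apply.** Inputs are the use rates in Appendix A. For the pilot: "Drug use at baseline and follow-up was 24% and 32%; alcohol use was 27% at both baseline and follow-up". Non-users = 1 − use rate; the count per branch is that share × 600.

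| Source | Alcohol use | Non-users (of 600) | Drug use | Non-users (of 600) |
| --- | --- | --- | --- | --- |
| Pilot, baseline | 27% | 73% (438) | 24% | 76% (456) |
| Pilot, follow-up | 27% | 73% (438) | 32% | 68% (408) |
| Study 2 | 28% | 72% (432) | 24% | 76% (456) |
| Study 3 | 22% | 78% (468) | 23% | 77% (462) |
| Study 1, six months | about 50% | about 50% (300) | 0.45 × 0.68 = 30.6% | 69.4% (416) |

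The ranges are 50-78% for alcohol and 68-77% for drugs. Three cautions apply:
- The Study 2 rates are explicitly for the last encounter. The Study 3 rates stand among last-encounter items, and the pilot sentence does not itself say that use was before sex.
- A last-encounter rate misses men who drank or used before other encounters, so it overstates the share with nothing to reduce over a period.
- Study 1 is the only source clearly tied to a period. It covers six months, whereas the trial asks about 60 days.

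**2. Dilution, as an illustration.** Assume an effect of d standard deviations among users, none among non-users, equal spread in both groups, 600 men per branch answering, and a two-sided level of 0.05/10 = 0.005. That level is the protocol's Bonferroni level for ten pairwise comparisons of primary outcomes; using it here is an assumption. With user share u:
- effect in the pooled mean = u × d
- power ≈ Φ(effect ÷ √(2/n) − 2.807), where n is the number analysed per branch

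With d = 0.4 and u = 0.27:
- All men: 0.27 × 0.4 = 0.108; √(2/600) = 0.0577; 0.108/0.0577 = 1.87; power = Φ(−0.94) ≈ 0.18.
- Users only: n = 0.27 × 600 = 162; √(2/162) = 0.111; 0.4/0.111 = 3.60; power = Φ(0.79) ≈ 0.79.

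Other values:

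| d | u | All 600 | Users only |
| --- | --- | --- | --- |
| 0.3 | 0.27 | 0.08 | 0.46 |
| 0.4 | 0.24 | 0.13 | 0.72 |
| 0.4 | 0.32 | 0.28 | 0.87 |
| 0.4 | 0.50 | 0.74 | 0.98 |
| 0.5 | 0.27 | 0.32 | 0.96 |

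In each case the smaller group of users is the more informative one. The sizes of effect are invented; only the direction should be relied on.

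**3. Count of items.** Appendix F prints six items and Appendix D announces six. Additional Measurements names alcohol and drug use among the topics. The outcome table counts four. The two that are missing are the two at issue here.

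**The case against.** The case against giving this much weight is strong, and most of it stands.

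- **No planned analysis is shown to be harmed.** The intention variables are listed as additional, and these two items are not on that list. No scoring rule for them is given, so it is an inference that *definitely won't* from an abstainer would count as the worst score.
- **The hypotheses do not depend on them.** The Aim 3 secondary hypotheses on alcohol and drug use before sex concern change between baseline and follow-up, measured by reported behaviour at both times.
- **The data can be rescued.** Study Instruments and Variables says that use before or during sex is asked at baseline, and the confidentiality section describes one study number across all three surveys. An analyst can restrict the items to baseline users, a group fixed before randomisation. That choice may properly sit in a statistical analysis plan, which is not at hand.
- **There is another immediate marker.** Clicks on the resource page, which carries drug and alcohol treatment links, are recorded after the post-intervention questions, and a comparison of treatment-link clicks by branch is foreseen.

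A reader might therefore infer too much in three ways: that the answers are uninterpretable, that these items are the only immediate signal on alcohol and drugs, or that most men certainly have no alcohol use to reduce. The first two are contradicted by the points above. The third fails because Study 1 puts alcohol non-use at only about half.

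What survives is that the form is fixed in this protocol and lacks a rule that it applies to a neighbouring item. Restriction at analysis also cannot classify men who decline the baseline questions on use.

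**Conclusion.** The point holds as a cheap improvement to an additional measure. The two items are put to men for whom they may have no meaning: about 68-77% for drugs, a majority in every source, and about 50-78% for alcohol, which is half or more. These ranges rest on earlier samples and mostly on last-encounter rates. A score pooled over all men would mix applicability with intention and shrink any effect in proportion to the share of users, if non-users do not respond.

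It would go too far to read this as a threat to the trial's conclusions. Primary and secondary outcomes are unaffected, and analysis among baseline users would recover much of the information. Separately, the count of four intention variables does not match the six items asked, and this needs to be reconciled whatever is done about routing.

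**What to change.** 1. In Appendix F, show the alcohol item only to men who reported alcohol before or during sex at baseline, and the drug item only to men who reported drugs before or during sex. The alternative is an added choice such as *does not apply, I do not drink/use before sex*, with those men left out of that score. Routing on baseline is the cleaner option, because a not-applicable answer is given after the man has seen his assigned content and could itself differ by branch.
2. State that branches are compared on these items within men who reported that use at baseline. Randomisation keeps these groups comparable.
3. In the outcome table, list all six intention items, or say why two are collected but not analysed, so that it agrees with Appendices D and F and with Additional Measurements.

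The cost is a skip rule of a kind already on the form and a few words in the table. The six-question text in Appendix D would no longer fit every man, but it already does not fit HIV-positive men, who are not shown the testing item. The comparison would rest on fewer men: about 132 to 300 per branch for alcohol and 138 to 192 for drugs on the rates above.
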